# A multi-center, randomized, double-blinded, parallel, placebo-controlled study to assess the efficacy and safety of Shenqisuxin granule in complex coronary artery disease after PCI: Study protocol

**DOI:** 10.3389/fcvm.2022.1000379

**Published:** 2022-09-12

**Keywords:** Shenqisuxin granule, complex coronary artery disease, percutaneous coronary intervention, cardiorespiratory fitness, randomized controlled trial

## Abstract

**Introduction:**

The Shenqisuxin granule (SQSX), a novel Chinese herbal formula, has the effect of preventing in-stent restenosis and improving angiogenesis. We intend to evaluate the efficacy and safety of SQSX to provide a possible therapeutic strategy for complex coronary artery disease (CCAD) after percutaneous coronary intervention (PCI).

**Methods/design:**

The study is a multi-center, randomized, double-blinded, parallel, placebo-controlled trial. A total of 120 participants will be randomized 1:1 into the intervention group and the control group. Based on standardized treatment, the intervention group and control group will receive SQSX and placebo for 2 months, respectively. The primary outcomes, metabolic equivalents (METS) and peak oxygen uptake (Peak VO_2_), and the secondary outcomes, including other indicators of cardiorespiratory fitness (CRF), the European Quality of Life Questionnaire (EQ-5D-5L), the Seattle Angina Scale (SAQ), etc., will be assessed at baseline and 2 months ± 3 days. In addition, the survey scales will also be tested at 1 month ± 3 days. Trimethylamine N-oxide (TMAO), high-sensitivity C-reactive protein (hs-CRP), and gut microbiota features will be assessed at baseline and 2 months ± 3 days to probe possible mechanism. The major adverse cardiac and cerebrovascular events (MACCE) and bleeding events will be monitored until the 12-month follow-up.

**Discussion:**

This study is launched to assess the efficacy and safety of SQSX in CCAD after PCI and probe the possible mechanism.

**Clinical trial registration:**

China Clinical Trial Registry, ChiCTR2200060979, Registered on June 14, 2022.

## Introduction

Complex coronary artery disease (CCAD), a lesion type with great difficulty and a low success rate in revascularization, is accompanied by a higher rate of major adverse cardiac and cerebrovascular events (MACCE) (1, 2). The 10-year mortality rate of three-vessel disease, chronic total occlusion, and left main lesion after percutaneous coronary intervention (PCI) is up to 21, 27.6, and 28%, respectively, much higher than the 18.6% for general lesions (3, 4). Therefore, one of the most urgent issues now is certainly how to reduce the incidence of MACCE.

Regarded as the fifth vital sign, cardiorespiratory fitness (CRF) reflects the body's ability to supply and utilize oxygen with the support of the circulatory and respiratory systems (5). The decline in CRF is commonly observed across the course of coronary artery disease (CAD) (6, 7). Currently, CRF is widely used for cardiac rehabilitation advice and prognosis assessment in CAD (5, 8). As gold standard indicators of CRF, the metabolic equivalents (METS) and peak oxygen uptake (Peak VO_2_) are both closely associated with MACCE. A 1-MET increment is associated with 13 and 15% decrements in the risk of all-cause mortality and major adverse cardiac events, respectively (9). The readmission rates and all-cause mortality can be predicted by Peak VO_2_ (10). Therefore, CRF could be used as a sensitive and reliable surrogate indicator to assess the incidence of MACCE. Several survey scales, including the European Quality of Life Questionnaire (EQ-5D-5L), the Seattle Angina Scale (SAQ), the Fatigue Severity Scale (FSS), and the Hamilton Anxiety Scale (HAMA), are used for evaluating the quality of life from different perspectives (11–14). Furthermore, the disturbed intestinal flora is associated with several CAD risk factors and contributes to atherosclerosis (15). In different stages of CAD, it's commonly accompanied by significant characteristic changes in the intestinal flora (16–18). The level of trimethylamine N-oxide (TMAO) is positively associated with the SYNTAX score II to quantify the complexity of CAD and causes an increased risk of MACCE (19, 20). We speculate that the intestinal flora and their metabolites could be potential targets for pharmacological effect.

The Shenqisuxin granule (SQSX) is a novel Chinese herbal formula for CAD under patent protection (Chinese patent number ZL202010122712.6). Our previous in-stent restenosis study in minipig has confirmed that the ingredients of SQSX prevent in-stent restenosis by inhibiting vascular smooth muscle cell proliferation (21). In addition, it also improves angiogenesis by activating the phosphatidylinositol 3-hydroxykinase-protein kinase B (PI3K-Akt) pathway and increasing the mRNA levels of vascular endothelial growth factor (VEGF) (22). At a time when CCAD is still a conundrum in the field of cardiovascular disease, we intend to evaluate the efficacy and safety of SQSX to provide a possible therapeutic strategy.

## Methods/design

### Study design

Approved by the Ethics Committee of Xiyuan Hospital, China Academy of Chinese Medical Sciences (CACMS) (Version No. CCAL-YJFA-3.0, December 15, 2021), the multi-center, randomized, double-blinded, parallel, placebo-controlled trial has been registered with the Chinese Clinical Trials Registry (ChiCTR2200060979). It is conducted under the guidelines of Good Clinical Practice and the Helsinki Declaration (23, 24). It adheres to the Standard Protocol Items: Recommendations for Interventional Trials Statements (SPIRIT) (25). The Consolidated Standards of Reporting Trials Extension for Chinese Herbal Medicine Formulas 2017 (CONSORT-CHM Formulas 2017) recommendations are strictly followed (26).

The trial is being conducted in four centers in China, including Xiyuan Hospital of CACMS, Dongzhimen Hospital of Beijing University of Chinese Medicine, the First Affiliated Hospital of Guangzhou University of Chinese Medicine, and the Affiliated Hospital of Shanxi University of Chinese Medicine. It consists of two main periods: a 2-month treatment and a 10-month follow-up. A total of 120 participants will be randomized 1:1 into the intervention group and the control group and then receive their respective interventions for 2 months. Figure 1 depicts the study's design.

**Figure 1 F1:**
[figure not shown]
Flow diagram of the study.

### Sample size estimation

The sample size was estimated based on METS. The study showed that after 8 weeks of cardiac rehabilitation, the METS increased from 3.9 to 4.6 in CAD patients after PCI (27). We assumed the mean METS value of 3.9 for the control group and 4.1 for the intervention group after treatment, with a standard deviation of 0.3 METS. With the type I error rate set at 0.05 and the type II error rate at 0.1, a sample size of 49 is required for each group with the use of PASS version 11. We will include 60 participants in each group, assuming that 20% of the participants are lost to follow up.

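### Sixty per group with 20% loss leaves 48 evaluable, one below the stated requirement of 49: a minor inconsistency that costs almost no power

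*Protocol article*

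**What the plan says.** The figures stand together in the protocol article under Sample size estimation.

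- **Endpoint:** "The sample size was estimated based on METS".
- **Effect:** "We assumed the mean METS value of 3.9 for the control group and 4.1 for the intervention group after treatment".
- **Spread:** the SD is taken as 0.3.
- **Error rates:** "With the type I error rate set at 0.05 and the type II error rate at 0.1".
- **Requirement:** "a sample size of 49 is required for each group", computed in PASS version 11.
- **Enrolment and loss:** "We will include 60 participants in each group, assuming that 20% of the participants are lost to follow up".

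The abstract gives the matching total: "A total of 120 participants will be randomized 1:1 into the intervention group and the control group". The Study design section repeats 120. The Statistical analysis section sets two-tailed testing at 0.05, with Student's t-test between groups when normality and equal variance hold and the Wilcoxon rank sum test otherwise.

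**The concern.** A loss allowance is meant to ensure that the number left after the assumed loss still meets the calculated requirement. Here the requirement, the loss rate and the enrolled number are all printed, and the enrolled number less the stated loss falls below the requirement. Since every figure is given, the mismatch cannot be put down to detail left to a fuller protocol or to an analysis plan that is not shown.

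What is at stake is mainly the coherence of the sample size justification, which readers check and which the final report will probably repeat. Power would be at stake too if the shortfall were large, so its size has to be worked out before the point is weighed.

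**Working it through.** **Inputs.** From Sample size estimation: means 3.9 and 4.1, so a difference of 0.2; SD 0.3; alpha 0.05; power 1 − 0.1 = 0.90; required number 49 per group; loss 20%; enrolled 60 per group. From Statistical analysis: two-tailed testing and the t-test. The sample size section does not state sidedness.

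**Step 1. Reproduce the 49.** The standardised difference is 0.2/0.3 = 0.667. With n per group, the two-sample t-test has 2n − 2 degrees of freedom and noncentrality 0.667 × √(n/2). The exact two-sided power from the noncentral t distribution is:

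| n per group | Noncentrality | Power |
|---|---|---|
| 48 | 3.266 | 89.84% |
| 49 | 3.300 | 90.43% |
| 60 | 3.651 | 95.17% |

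The unrounded requirement is 48.26, so 49 is the smallest whole number that reaches 90%. The plan's figure is confirmed.

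The normal approximation gives 2 × [0.3 × (1.960 + 1.282)/0.2]² = 47.28, so 48 per group. Its one-sided version gives 39. The stated 49 is therefore the exact two-sided t-test answer, consistent with the test named in Statistical analysis.

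**Step 2. Apply the stated loss to the stated enrolment.** 60 × (1 − 0.20) = 48 per group, or 96 in all. The requirement is 49 per group, or 98 in all. The shortfall is one per group.

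**Step 3. Inflate the requirement for the stated loss.** 49/(1 − 0.20) = 61.25, rounded up to 62 per group, or 124 in all. The plan has 60 and 120.

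**Step 4. Find the loss that 60 per group can absorb.** 60 − 49 = 11, and 11/60 = 18.3%. A 20% loss is 12 of 60.

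**Step 5. Put the gap in terms of power.** At 48 per group, power is 89.84%, which is 0.16 percentage points below 90%. The type II error is 10.16% against the planned 10%. By the normal approximation, power at 48 is 90.42%.

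**The case against.** The strongest reply is that nothing of substance is lost. Power at 48 per group rounds to 90%, and a type II error of 10.16% is 0.1 at the precision the article uses. Under the normal approximation, 48 is itself the required number, so 48 against 49 is no more than the gap between two standard formulas. The 20% is a round planning figure, and the uncertainty in it and in the SD of 0.3 is likely to outweigh one participant per group. All of this stands as an argument about size. It does not make the figures agree: the plan prints 49, which is the t-test answer, and the t-test is the comparison it names.

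A second reply is that the 20% has no time point. METS is measured at Visit 3, at 2 months, while follow-up runs to 12 months. If the 20% covers the whole year, fewer than 12 of 60 may be missing when METS is measured, and 49 or more could remain. The intention-to-treat set is all randomised participants, and how missing values enter that analysis may be set out elsewhere. This is fair, and it makes the shortfall conditional on reading the 20% as loss of the METS measurement. That is the natural reading of an allowance attached to a METS calculation, and the article gives no other.

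A reader might also infer how 60 arose, for instance by adding 20% to 49 (49 × 1.2 = 58.8) and rounding up. The article shows no inflation step, and rounding 61.25 down, or calling 18.3% loss 20%, would fit as well. The origin is unknown, and the point does not depend on it.

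**Conclusion.** The inconsistency is real but minor. On the plan's own inputs, 60 per group with 20% loss leaves 48, one below the stated 49, and power by the two-sided t-test is 89.8% against a target of 90%.

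A reader might infer that the trial is underpowered or fails to deliver its planned power. The documents do not support that in any material sense: the deficit is 0.16 percentage points at the assumed loss, and there is none if 11 or fewer per group are lost.

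A reader might equally suppose that adjusting for baseline METS would more than make up the shortfall. The article provides for analysis of covariance if necessary, but it gives no correlation between baseline and post-treatment METS, so that gain cannot be sized from the document.

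The conclusion assumes the stated difference of 0.2, the SD of 0.3, a t-test on METS, and 20% loss by the time METS is measured. Whether that difference and SD are realistic is not judged here.

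**What to change.** Keep 120 participants and reword the last sentence of Sample size estimation in one of two ways:

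- 60 per group allows for about 18% loss (11 of 60) while keeping 49 evaluable per group and 90% power; or
- with 60 per group, a 20% loss leaves 48 evaluable per group, with 89.8% power by the two-sided t-test.

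The cost is one sentence and a slightly less favourable loss allowance or power figure. Enrolment, randomisation and analysis do not change. Raising enrolment to 62 per group would also remove the mismatch, but four more participants are hard to justify for 0.16 percentage points of power.

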### Inclusion criteria

The study will include patients who satisfy all of the following inclusion criteria:

(1) Diagnosis of CCAD based on one or more of the following coronary artery lesions (28–30):

Bifurcation lesions (side branch diameter >2.0 mm);Excessive tortuosity of proximal segment;Severe coronary artery calcification;Chronic total occlusion lesions (>3 months);Left main lesion;Aorto-ostial lesions;Diffuse lesions (>20 mm length);Multivessel coronary artery stenosis (≥2 two vessels);Extremely angulated lesions (>90° bend);In-stent restenosis.

(2) Diagnosis of stable angina according to the 2019 ESC guidelines (31);(3) NYHA class I-III;(4) At least one stent was implanted within 2 years;(5) 18 years ≤ age ≤ 75 years;(6) Diagnosed as the traditional Chinese medicine (TCM) syndrome of the Qi deficiency in the heart and spleen according to an array of specific symptoms, including chest tightness, abdominal distension, appetite loss, fatigue, and lassitude, with a pale tongue and a white greasy coating, etc., (32);(7) No antibiotics, hormones, laxatives, antidiarrheals, or probiotics have been used within 3 months;(8) Written informed consent is obtained.

### Exclusion criteria

Patients should be excluded if any of the following exclusion criteria are fulfilled:

(1) Renal insufficiency (serum creatinine >220 umol/l for males or >175 umol/l for females);(2) Severe liver disease or elevated alanine transaminase (ALT) and aspartate transaminase (AST) (≥3 times upper limit of normal);(3) Controlled systolic blood pressure or controlled diastolic blood pressure >160/100 mmHg, respectively;(4) Glycosylated hemoglobin ≥9.5% or random blood glucose ≥13.7 mmol/L in diabetics;(5) Women who are pregnant, are breastfeeding, or are planning to become pregnant;(6) Acute or chronic severe cerebrovascular disease;(7) Malignancies;(8) Severe hematopoietic disorders;(9) Severe mental illness;(10) Intestinal inflammatory or malabsorptive disorders;(11) Patients who have participated in other studies within 3 months.

### Withdrawal, dropout, and discontinuation

Participants can withdraw from the study whenever they want. The trial will be discontinued in the events of the following: (1) the continuation of the trial is detrimental to participants; (2) a serious adverse reaction occurs; (3) the participant's poor compliance. The cause of withdrawal will be recorded.

### Randomization and blinding

Stratified by center, sex, and age with a 1:1 allocation using random block sizes of 6, the randomization sequence was created using SAS software version 9.4. The investigators, patients and data analysts are blinded to the randomization sequence and treatment assignment. The emergency letter has been prepared, and the reason for opening the letter will be recorded if investigators break the blind.

### Intervention

All participants will receive standardized treatment based on the 2019 ESC guidelines (26), which includes antiischemic therapy, antiplatelet therapy, statins, etc. Furthermore, the intervention group and control group will receive SQSX and placebo for 2 months, respectively. The composition of SQSX is shown in Table 1. The placebo consists of 5% SQSX and 95% dextrin and is similar in odor and shape to the active granule. The SQSX and placebo were manufactured by the Department of Pharmaceutics of Xiyuan Hospital. The drug number is printed on the package of SQSX and placebo. The subjects will be instructed to take the granules after breakfast and supper (15 g per sachet, 1 sachet each time, twice daily). The granules will be supplied and/or recycled at each visit to verify compliance. During the trial, other medicines with an influence on the intestinal flora are forbidden.

**Table 1 T1:** The composition of SQSX.

**Herb**	**Latin name**	**Dosage (g)**
Huang Qi	Astragali Radix	30
Dan Shen	Salviae Miltiorrhizae Radix Et Rhizoma	15
E zhu	Curcumae Rhizoma	9
Dang Gui	Angelicae Sinensis Radix	6
Bai Zhu	Atractylodis Macrocephalae Rhizoma	6
Huang Lian	Coptidis Rhizoma	5

### Study visits and follow-up

It begins with a 7-day lead-in period in which eligible participants sign informed consent. The baseline data will be gathered at Visit 1. Visits 2 and 3 will occur 1 month ± 3 days and 2 months ± 3 days following treatment, respectively. The follow-up will be conducted at 6 months ± 7 days and 12 months ± 7 days. Table 2 shows the evaluation schedule in detail.

**Table 2 T2:** Measurement items and points of data capture.

	**Lead-in period**	**Treatment period**			**Follow-up period**	
	**Screening**	**Visit 1**	**Visit 2**	**Visit 3**	**Follow-up 1**	**Follow-up 2**
	**(-7D ~−1D)**	**(-1D ~0D)**	**(1M ±3d)**	**(2M ±3d)**	**(6M ±7d)**	**(12M ±7d)**
**Patients**						
Eligibility screen	×					
Informed consent	×					
General information^a^	×					
Medical history^b^	×					
Allocation	×					
**Intervention**						
Intervention group						
Control group						
**Outcomes**						
CPET^c^		×		×		
EQ-5D-5L		×	×	×		
SAQ		×	×	×		
FSS		×	×	×		
HAMA		×	×	×		
BSSS		×	×	×		
Echocardiography		×		×		
Electrocardiography		×		×		
TMAO		×		×		
hs-CRP		×		×		
Stool collection and metagenomic sequencing		×		×		
Safety indicators^d^		×		×		
MACCE and bleeding events^e^			×	×	×	×
**Others**						
Drug distribution/recycle		×	×	×		
Combined medication		×	×	×	×	×
AEs			×	×	×	×

a General information includes: name, date of birth, gender, ethnicity, employment status, etc.

b Medical history includes: current medical history of CCAD and past history.

c CPET: METS, Peak VO_2_, VO_2_/HR, AT, VE/VCO_2_ slope, etc. will be used to evaluate CRF.

d Safety indicators include: routine tests of blood, urine, stool, and the function of the liver, kidney, and coagulation.

e MACCE include: death, non-fatal myocardial infarction and ischemic stroke.

#### Secondary outcomes

The first of the secondary outcomes are other indicators of cardiopulmonary exercise testing (CPET), including the oxygen pulse (VO_2_/HR), the anaerobic threshold (AT), and the slope of ventilatory equivalent for carbon dioxide (VE/VCO_2_ slope), etc. The additional secondary outcomes are: (1) EQ-5D-5L; (2) SAQ; (3) FSS; (4) HAMA; (5) the blood stasis syndrome score (BSSS) (34); (6) echocardiography; (7) electrocardiography; (8) TMAO; (9) high-sensitivity C-reactive protein (hs-CRP); (10) MACCE and bleeding events. Furthermore, metagenomic sequencing will be performed to probe possible changes to the structure of intestinal flora after treatment. The plasma and stool samples will be collected and stored in the laboratory freezer (−80°C) for future TMAO testing and metagenomic sequencing.

#### Safety

Safety indicators, including routine tests of blood, urine, stool, and the function of the liver, kidney, and coagulation, will be performed at Visit 1 and Visit 3. All outcome measures are listed in Table 3 in detail.

**Table 3 T3:** Primary, secondary and safety objectives.

**Objectives**	**Outcome measures**
**Primary objective**	
To determine whether SQSX is superior to placebo in improving patient's CRF.	Changes in METS and Peak VO_2_ after treatment.
**Secondary objectives**	
To determine whether SQSX is superior to placebo in improving patient's CRF.	Changes in other indicators of CPET, including VO_2_/HR, AT, and VE/VCO_2_ slope, etc. after treatment.
To compare the effect of SQSX vs. placebo on quality of life based on several survey scales.	Changes in scores measured by EQ-5D-5L, SAQ, FSS, and HAMA from baseline.
To compare the effect of SQSX vs. placebo on TCM syndrome.	Change in BSSS from baseline.
To assess cardiac structure and function with echocardiography and electrocardiography.	Results will be reported separately.
To explore the possible impact of SQSX on TMAO.	Change in TMAO after treatment.
To explore the possible impact of SQSX on hs-CRP.	Change in hs-CRP after treatment.
To depict intestinal flora features of CCAD and explore possible changes induced by SQSX.	Changes to the structure of intestinal flora after treatment using metagenomic sequencing.
To determine whether SQSX is superior to placebo in reducing the incidence of MACCE and bleeding events.	Time to the first occurrence of any of the components of this composite: (1) death; (2) non-fatal myocardial infarction; (3) ischemic stroke; (4) bleed.

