**Safety objectives**	
To evaluate the safety of SQSX for CCAD after PCI.	(1) Changes in routine tests of blood, urine, stool, and the function of the liver, kidney, and coagulation; (2) AEs.

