### Statistical analysis

An independent statistician will be responsible for data analysis. The enrolling results and the causes of missing data will be detailed. The efficacy analysis will be performed based on the intent-to-treat (ITT) and per-protocol (PP) populations. The ITT set consists of all participants randomized, and the PP set includes participants who follow the protocol exactly with an adherence rate of at least 80%. The primary outcomes, METS and Peak VO_2_ after 2 months of treatment, and the secondary outcomes, the change values of VO_2_/HR, AT, VE/VCO_2_ slope, several survey scales (SAQ, EQ-5D-5L, HAMA, FSS, etc.), TMAO, and hs-CRP from baseline to each visit, are both quantitative data. Others, including the incidence of MACCE and bleeding events, are qualitative data. The quantitative data will be presented as means ± SD, 95% confidence intervals, median and interquartile range. For inter-group comparison, if both groups meet the normal distribution with equal variance, the Student *t*-test will be applied, otherwise, the Wilcoxon rank sum test will be used. For within-group comparison, the Wilcoxon signed rank test or paired *t*-test will be adopted. The qualitative data will be described using frequency and rate. The Fisher's exact probability test and the McNemar test will be applied for inter-group comparison and within-group comparison, respectively. Confounding factors will be balanced using analysis of covariance if necessary. The linear mixed-effects model will be used to analyze longitudinal data. For safety analysis, the details of AEs will be tabulated and the incidence will be compared further. The above analysis will be conducted based on SAS software version 9.4. In all analyses, a two-tailed *P*-value < 0.05 will be regarded as statistically significant.

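### Change in TMAO is tested without prespecified adjustment, although baseline TMAO and kidney function are both collected: a loss of precision and a weak basis for mechanistic attribution, not bias

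*Protocol article*

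**What the plan says.** **Objective and outcome.** Table 3 lists the secondary objective "To explore the possible impact of SQSX on TMAO", with the outcome measure "Change in TMAO after treatment".

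**Framing.** The Abstract says that TMAO, hs-CRP and "gut microbiota features will be assessed at baseline and 2 months ± 3 days to probe possible mechanism". The Introduction adds: "We speculate that the intestinal flora and their metabolites could be potential targets for pharmacological effect". TMAO is the only such metabolite that the article names.

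**Analysis.** The Statistical analysis section lists TMAO among the quantitative outcomes analysed as change from baseline. Arms are compared by Student t-test if normality and equal variance hold, otherwise by Wilcoxon rank sum test. Within-group tests are also planned. On covariates the section says only "Confounding factors will be balanced using analysis of covariance if necessary".

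**Kidney function.** The exclusion criterion is "Renal insufficiency (serum creatinine >220 umol/l for males or >175 umol/l for females"), so values up to those limits are admitted. The Safety section states that tests including "the function of the liver, kidney, and coagulation, will be performed at Visit 1 and Visit 3". Table 2 places TMAO at the same two visits. In Table 3, kidney function appears only as a safety outcome: "Changes in routine tests of blood, urine, stool, and the function of the liver, kidney, and coagulation". Randomization is stratified by center, sex and age, not by renal function.

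**The concern.** There are two weaknesses, and neither invalidates the randomized comparison.

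**Precision.** A test on the change score is less precise than an analysis of the Visit 3 value adjusted for the baseline value, unless the two visits correlate almost perfectly. The covariance clause could recover this, but it names no outcome, no covariate and no trigger. As worded, adjustment can be decided after the data are seen.

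**Attribution.** If plasma TMAO depends partly on renal clearance (an assumption from general physiology, stated nowhere in the article), a change in kidney function during the 2 months could move TMAO with no change in the flora. The information needed to judge this is collected at the same visits, but the plan does not link it to the TMAO result. The within-group tests are more exposed than the between-arm test, because randomization does not protect a before-after comparison from drift in renal function.

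**Working it through.** **1. The plan's own figure.** The article gives no TMAO standard deviation, correlation or target difference. Its only sample-size figure is for METS: 3.9 against 4.1, SD 0.3, two-sided 5%, power 90%.
- Normal approximation: 2 × (1.960 + 1.282)² × (0.3/0.2)² = 2 × 10.51 × 2.25 = 47.3, so 48 per group.
- The t-based solution is 48.26, so 49 per group. The stated 49 is reproduced, but it says nothing about TMAO.
- With 60 per arm and 20% loss, 60 × 0.80 = 48 completers per arm, used below.

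**2. Is the unadjusted between-arm test biased by baseline renal function?** No.
- In 20,000 simulated trials with 48 per arm and no treatment effect, the t-test rejected in 0.052, 0.052 and 0.050 of trials when baseline renal function correlated with TMAO change at 0, 0.3 and 0.5.
- The standard error of a chance imbalance is √(2/48) = 0.204 SD, so 95% of imbalances lie within 1.96 × 0.204 = 0.40 SD.
- With an assumed correlation of 0.1 to 0.5, this moves the TMAO contrast by at most 0.04 to 0.20 SD. That is part of the sampling error the test already allows for.

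**3. Precision from baseline TMAO.** Assume equal variance σ² at both visits and a within-patient correlation r, on the log scale.
- Variance of the change score: 2σ²(1 − r).
- Residual variance after adjusting for baseline: σ²(1 − r²) = σ²(1 − r)(1 + r).
- Ratio: (1 + r)/2. For r = 0.3, 0.5 and 0.7 this is 0.65, 0.75 and 0.85.
- The detectable difference at 80% power is 2.80 × 0.204 = 0.57 SD of the change score. Adjusted, it is 0.57 × √0.65 = 0.46 to 0.57 × √0.85 = 0.53, in the same unit.

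**4. Precision from baseline kidney function.** With an assumed correlation r between baseline renal function and TMAO change, the variance left is 1 − r².

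| r (assumed) | variance left | detectable difference (0.57 SD unadjusted) |
|---|---|---|
| 0.1 | 99% | 0.57 SD |
| 0.3 | 91% | 0.55 SD |
| 0.5 | 75% | 0.50 SD |

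These factors should not be multiplied by those in step 3, because baseline TMAO may already carry part of the renal information.

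**5. Attribution.** Suppose that treatment shifts renal function by 0.2 to 0.5 SD, that renal change correlates with TMAO change at 0.3 to 0.5, and that there is no flora effect (all assumed).
- Induced TMAO shift: 0.2 × 0.3 = 0.06 SD to 0.5 × 0.5 = 0.25 SD.
- Probability of a significant result in that direction: 1 − Φ(1.96 − shift/0.204). For 0.06 this is 1 − Φ(1.67) = 0.048; for 0.25 it is 1 − Φ(0.735) = 0.23.
- The formula counts one direction only, so the figure to compare with is 0.025. The false lead ranges from slight to moderate, and the article has no data to place it within that range.

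**The case against.** The case for leaving the plan alone is strong in several respects.

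- **Tentative wording.** A reader might infer that the protocol will read any TMAO change as proof of a flora mechanism. It does not say so. The Table 3 row only explores an impact, the Abstract speaks of a possible mechanism, and the Introduction speculates. Flora is also measured directly by metagenomic sequencing under its own objective, so the mechanism question does not hang on TMAO.
- **Validity.** A reader might infer that the wide creatinine limits confound the comparison. They do not. Randomization protects it (step 2), and a change score already removes most stable differences between patients. The limits describe who is eligible; the article does not give the renal function of those enrolled.
- **Visibility.** Change in kidney function is a stated safety outcome at the same visits, so a renal shift would not be hidden.
- **Unseen documents.** The covariates for an exploratory biomarker are often left to the full protocol or analysis plan, neither of which is shown.
- **Outside premise.** The renal dependence of TMAO is in no part of the article.

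All of this stands and limits the point to low priority. What remains is that the article does fix a test on change and does leave adjustment to an open condition. The gain from baseline TMAO needs no renal premise. The sentence on mixed models for longitudinal data does not close the gap either, because it names no outcome and no handling of baseline.

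**Conclusion.** The point holds as a low-priority improvement. The between-arm TMAO comparison is valid as planned; it is less precise than it could be, and it gives a weak basis for naming a mechanism.

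Adjustment for baseline TMAO would leave 65% to 85% of the change-score variance. This rests on an assumed within-patient correlation of 0.3 to 0.7 and equal variance at the two visits. The comparison is with a t-test on change; the Wilcoxon alternative was not evaluated. The extra gain from creatinine could be anything from negligible to useful and rests on an assumed TMAO-renal correlation. The attribution risk in step 5 rests on assumed shifts and correlations throughout.

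The documents do not support the stronger conclusions that the TMAO test is biased or that the mechanism question cannot be answered.

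**What to change.** 1. **Prespecify the TMAO analysis.** Use ANCOVA of log TMAO at Visit 3 with arm, baseline log TMAO and baseline creatinine (or eGFR) as terms. For this outcome it replaces both the test on change and the conditional covariance clause. State that including creatinine rests on an assumed link between TMAO and renal function.
2. **Report creatinine change by arm beside the TMAO result**, not only in the safety tables.
3. **Use adjustment for creatinine change only as a descriptive sensitivity analysis.** It is a post-randomization variable that treatment may affect, so conditioning on it can itself introduce bias.
4. **State how the result will be read.** A TMAO difference alone does not establish a flora mechanism; it is interpreted together with the renal and metagenomic results. Do not make attribution to the flora depend on finding no between-arm difference in creatinine change. With about 48 completers per arm, a null result there is not evidence of no effect.

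The cost is analysis wording only. All values are already collected at Visits 1 and 3, and no patient, visit or assay is added.
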